### Intervention

The cognitive-behavioral intervention aims at modifying the dysfunctional beliefs in order to appropriately deal with care activities. It is based on the theoretical principles of the cognitive theory, which assumes that specific thoughts and beliefs may trigger negative emotions and unsettled behavior. This program offers the possibility to train cognitive-behavioral capacities and strategies to confront negative feelings and emotions (guilt, sadness, anger) and to change or eliminate certain negative beliefs and thoughts that serve as barriers or obstacles that hinder appropriate care [13,14].

#### Main sessions and contents of the cognitive-behavioral program

Session 1.-Presentation of the program: Introducing the Stress Model

Session 2. Necessity of self-care and introducing the concepts of thought, emotion and situation. Taking into account the necessity of caring, the relation among thought, emotion and conduct, and the differences among these concepts.

Session 3. Learning the cognitive model and differentiating among thought, emotion and situation. Distinguishing the concepts of situation, thought and emotion, the concept of automatic thoughts. Influence of one's body and body states on one's feelings

Session 4. Analyzing the errors of thought. Introducing the importance of pleasant activities.

Session 5.-Learning to adapt our thoughts to reality and to plan pleasant activities. Review of the previous session (errors of thought). Relation between daily activities and state of mind.

Session 6. Intervention in cognitive barriers: "you should". Feelings of guilt and the role of society on these cognitive barriers (errors of thought): What does the "you should" phrase mean and why it is important. Identifying the "you should" phrases, different forms they may take, where they come from and how they have been formed.

Session 7. Knowing our rights and learning to ask for help: personal "you should" phrases, implementing the "you should" phrase, analyzing and discussing the caregivers' rights and the difficulties in applying them into their lives; difficulties in asking for help.

Session 8.-Knowing our rights and learning to ask for help (II): How to ask for help and review.

A coordination system will also be established between the Health Care Center professionals (cotherapists) and the psychologists of the Mental Health Units (therapists) in order to provide caregivers with the necessary help for the specific interventions of the project.

### Measurements

#### 1.Sociodemographic variables

The initial assessment protocol of the caregivers comprises the following sociodemographic variables associated with care: age and sex of the caregivers and the person under care; relationship or kinship with the person under care; number of months and daily hours dedicated to the tasks related with care; cause of the dependence; family members the person under care lives with; help received from relatives, friends or institutions; and characteristics of the caregiver (educational level, professional activity, marital status, consumption of antidepressant or anti-anxiety agents, state of health, income). The type of disease that causes the dependence is also assessed, the dependence degree of the patient through the Barthel Index (which evaluates the dependence for the basic activities of the daily life) and the Pfeiffer Test (to assess the cognitive deterioration).

#### 2. Result Variables

Variables will be assessed before the intervention and after six months of the first assessment. Questionnaires in Spanish will be used as determined by the validations performed in the Primary Health Care System. The following questionnaires are to be used:

a) Family functionality perceived by the caregiver was evaluated with the Family APGAR Questionnaire validated in Spain [15]. This questionnaire rates satisfaction with family relations and distinguish five components of the family function: adaptability, partnership, growth, affection and resolve. It consists of the five questions, with three possible answers: 0 ("hardly ever"), 1 ("sometimes"), 2 ("always"). The total score range varies from 0 to 10, meaning the higher total score, the better family functioning. A global score of 7 points or more indicates family functionality, while a score of less than 7 points indicates family dysfunction. The internal consistency (Cronbach's alpha) of this questionnaire in this study was 0.77.

b)The Short Zarit Interview used in palliative care cases to determine the family giving up has an S of 100%, Sp 90.5%, PPV 95.45%, and NPV 100% in defining caregivers' burden in primary care [16].

c) Quality of life was evaluated with Ruiz and Baca's Questionnaire (1993) [17]. This is made up of 39 items each with a Likert-type five-point scale comprising four dimensions: social support, general satisfaction, physical/mental well-being, work overload and free time. This study gave an internal consistency index (Cronbach's alpha) of 0.94.

d) Social support: in order to measure caregivers' perception of the amount and type of personal social support they receive, the 11-item version [18] of the Duke-UNC Functional Social Support Questionnaire [19] was used. Response options to the items (for example, ''I get love and affection'') are on a 5-point scale ranging from 1 (''much less than I would like'') to 5 (''as much as I would like''). The scale had good internal consistency (Cronbach's a = 0.82).

e) Mental health: caregiver's mental health was measured with the 12-item version of the General Health Questionnaire (GHQ-12) [20], one of the most extensively used screening instruments for common mental disorders. Items (for example, ''being able toconcentrate on whatever you are doing'') are rated by caregivers on a 4-point Likert-type scale, ranging from 0 (''better than usual'', ''not at all'' or ''more than usual'') to 3 (''much less than usual'', ''much more than usual'' or ''much less than usual''). The scale hadgood internal consistency (Cronbach's a = 0.83).

f) Dysfunctional thoughts about caregiving: the dysfunctional thoughts about caregiving questionnaire (DTCQ) [13,14] is a 16-item measure developed following cognitive behavioral principles that assesses caregivers' thoughts that may act as barriers or obstacles to an adaptive coping style with regard to caregiving (e.g., 'A good caregiver should never get mad or lose control with the person who is being cared for'). Responses are coded on a Likert scale that ranges from 0 ('totally disagree') to 4 ('totally agree'). In this questionnaire's development study, this scale showed a 3-month test-retest reliability of 0.60 and a correlation of 0.59 with a brief version of the Dysfunctional Attitudes Scale developed by Andrews, Lewinsohn, Hops, and Roberts (1993). Good internal consistency was found for this scale in this study (Cronbach's alpha 0.90).

#### 3. Implementation measures of the intervention

A variety of assessment procedures has been designed of the achievements accomplished with the program, during the sessions and during the sessions intervals. These procedures aim at responding to three key questions associated with each of the aspects of the intervention implementation defined in the works by Zarit y Leitsch (2001) [21]:

##### 3.1.-Did you understand the concepts mentioned in the program? (Transmission of information)

As part of the satisfaction questionnaire of the program, to be completed anonymously and to be delivered during the last session of the program, caregivers are required to inform how satisfied they are with the content of the sessions, if these were clearly presented, if the number of sessions is sufficient, etc.

##### 3.2.- Did you learn the capacities and techniques taught during the sessions? (Reception of intervention)

The assessment of how the information is received will be carried out by registering the attendance to each session, as well as with a questionnaire specifically designed for this program. The questionnaire serves to assess if after intervention caregivers believe that their knowledge or capacities have increased so as to understand or confront the key aspects the program focuses on.

##### 3.3. - Were techniques and capacities appropriately used in the specific care context? (Generalization of intervention)

Two procedures have been designed to evaluate the completion of the registries the caregivers are required to do as "homework". The first procedure exclusively assesses whether registries have been performed according to the criteria established to this end. The second procedure quantitatively assesses the completion of the main registry provided to the caregiver as "homework", in compliance with the mentioned criteria. This is the most important task to the fulfillment of the objectives included in the program. Moreover, it is the sole task required in all sessions from the beginning of the program to its completion. It refers to the registries related to the differences among situation, thought and emotion, which lead to the 5-column technique (modification of thought).

#### 4. Qualitative information

Besides the aforementioned assessment procedures, both the main therapist and the cotherapist will gather qualitative information relevant to the program objectives and likely to contribute data about the results obtained during the intervention, data which was not accurately registered with the other procedures. The collection of the additional information has been recommended by authors such as Zarit and Leitsch (2001) [21].

### Organization of data collection

The data registered by the researcher will be reviewed by the study instructor so as to detect lacking information or inconsistencies in the data. Lacking information or inconsistencies in the variables included in the protocol will be recovered when possible by the study instructor. The instructor can only alter the original information reported by the researchers once the correction signed by the corresponding researcher becomes available. Once the information has been recovered, the database will be validated in order to assure its quality. Lastly, the data analysis will start. The database is the property of the Research Unit of La Alamedilla.

### Statistical analysis

Data input will be made using the Teleform system (Autonomy Cardiff Vista, California, USA), with a questionnaire previously designed for the project, and exporting the data to the SPSS version 15.0 statistical package (SPSS Inc., Chicago, Illinois, USA) for posterior analysis.

A first descriptive analysis of the socio-demographic characteristics of the study groups will be made. The data will be presented with the mean and standard deviation in the case of quantitative variables, and as frequency distributions for qualitative variables. The Pearson chi-squared test will be used to analyze associations between qualitative variables. The Student t-test for independent samples will be used to compare the means for the two groups. In turn, the analysis of repeated measures will be based on the McNemar test for qualitative data and the Student t-test for paired data in application to quantitative data.

In order to describe the characteristics and intensity of the caregivers' analyzed variables, the sum of the grades as well as its mean will be used, so as to compare the range of grades and make their interpretation easier. Analyzing the impact of the intervention will be carried out through intent to treat analysis.

The contrasting hypothesis will establish an alpha risk factor of 0.05 as the limit of statistical significance.

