### Study population

The study will be carried out at the Primary Health Care System in urban areas. The study subjects will be adults both male and female living near two health centers in the city of Salamanca (La Alamedilla, Miguel Armijo), an estimated population of 42.000 residents. The health care professionals of both centers will offer the caregivers of dependent relatives the opportunity to participate on the study. Once the informed consent is signed, a researcher will complete the preintervention assessment by means of an individual interview.

The sample size is expected to reveal a difference of or superior to 12 units on the Ruiz-Baca's quality of life questionnaires between the intervention group and its control. With an estimated alpha risk 0.05 and a beta risk 0.20 in a bilateral contrast, 73 subjects are required in the first group and 73 in the second one. The common standard deviation assumed is 25.7 from a previous study.

Through consecutive sampling, 150 caregivers will be included, who are responsible for almost all the care given to dependent and ill relatives who receive health care in the centers. One half will be randomly assigned to the trial group and the other half to the control group in a waiting list format. Those in the control group will be offered to participate in the therapy sessions, but only once the intervention and final assessment of the first group have been completed. Those in the intervention group will be divided into groups of 8 and 12 subjects for the group sessions.

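### The between-arm comparison is an unadjusted t-test although the outcomes are measured at baseline; adjusting for the baseline score would gain power at no cost, by an amount that depends on a correlation the protocol does not give

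*Protocol article*

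**What the plan says.** The Statistical analysis section of the protocol article gives the between-arm method for quantitative variables in one sentence: "The Student t-test for independent samples will be used to compare the means for the two groups". For repeated measures it adds only the McNemar test and the paired t-test, which are comparisons within subjects. The impact of the intervention is to be analysed by intention to treat. No baseline-adjusted model is named.

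Under Measurements, 2. Result Variables, the timing is: "Variables will be assessed before the intervention and after six months of the first assessment". Each scale therefore has a baseline value from the same instrument.

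The sample size in Study population is a plain comparison of two means, with a target difference of 12 units on the Ruiz-Baca questionnaire, a two-sided alpha of 0.05 and 80% power. The stated result is that "73 subjects are required in the first group and 73 in the second one". As to variability, the section reads: "The common standard deviation assumed is 25.7 from a previous study". It does not say whether that SD belongs to the score or to its change. The Methods/Design part of the abstract describes change in caregivers as the principal measure, and the t-test sentence does not say whether it is applied to six-month scores or to changes.

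**The concern.** A baseline value of the same scale is usually among the best predictors of its follow-up value. A t-test on six-month scores leaves that information unused. A t-test on change scores uses it with a fixed weight of one, which adds noise when the baseline to follow-up correlation is below 0.5. ANCOVA estimates the weight from the data, so in large samples it is at least as precise as either.

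The protocol fixes neither which score is tested nor what 25.7 measures, so the power of the planned analysis depends on two unstated choices. Precision also matters in this trial. The Limitations section concedes that the sample may be too small for definitive results, and recruiting 150 leaves only 150 − 146 = 4 caregivers above the stated requirement.

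**Working it through.** **Inputs from the protocol article.** Difference 12 units, SD 25.7, two-sided alpha 0.05, power 80%, 73 per arm (Study population). Outcomes at baseline and six months (2. Result Variables).

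**Assumed input.** The baseline to six-month correlation r of the Ruiz-Baca score is not given. I use 0.3, 0.5 and 0.7. The only retest figure in the article is 0.60 over three months, for the dysfunctional thoughts scale. It concerns another instrument and a shorter interval, so it does not fix r here.

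**Step 1. Reproduce the plan's figure.** n per arm = 2 × (1.960 + 0.842)² × (25.7/12)² = 72.0 by the normal approximation (72.001, rounded up to 73). With the noncentral t distribution, n = 72.97, again 73. Power at 73 per arm is 80.0%. The stated sample size is correct for an unadjusted t-test.

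**Step 2. Take 25.7 as the SD of the score** (assumed equal at both times). The SD that governs each analysis is:
- six-month t-test: 25.7
- change-score t-test: 25.7 × √(2(1 − r))
- ANCOVA: 25.7 × √(1 − r²)

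At r = 0.5, for example, ANCOVA has SD 25.7 × √0.75 = 22.26. The standard error is 22.26 × √(2/73) = 3.68, and 12/3.68 = 3.26. Noncentral t power at 73 per arm, with one degree of freedom spent on the covariate:

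| r | six-month t-test | change-score t-test | ANCOVA (SD) |
|---|---|---|---|
| 0.3 | 80% | 66% | 84% (24.52) |
| 0.5 | 80% | 80% | 90% (22.26) |
| 0.7 | 80% | 95% | 97.5% (18.35) |

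In sample-size terms, ANCOVA at r = 0.5 reaches 80% power with 55 per arm.

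**Step 3. Take 25.7 as the SD of change.** The score SD is then 25.7/√(2(1 − r)), and the ANCOVA SD is 25.7 × √((1 + r)/2).

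| r | six-month t-test (score SD) | change-score t-test | ANCOVA (SD) |
|---|---|---|---|
| 0.3 | 91% (21.72) | 80% | 94% (20.72) |
| 0.5 | 80% (25.70) | 80% | 90% (22.26) |
| 0.7 | 58% (33.18) | 80% | 86% (23.69) |

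**Step 4. Compare.** In every row of both tables ANCOVA has the highest power. If r were 0 and 25.7 the score SD, ANCOVA would still have 80.0%, so the spent degree of freedom costs essentially nothing.

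None of these powers allows for dropout or for correlation among caregivers treated in the same therapy group.

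**The case against.** The strongest reply is that nothing here is wrong. An independent-samples t-test is valid in a randomised trial, it matches the method used for the sample size, and covariate adjustment is often left to an analysis plan that is not shown. The first two parts stand, and they make this a matter of efficiency. The third does not remove the point, because the article does not leave the method open: it names a specific unadjusted test.

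A reader might also draw stronger conclusions that the article does not support:

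- **That ANCOVA would lift power to 90%.** This needs r of about 0.5 (0.49 at 73 per arm), which the article does not give. Only the range can be stated.
- **That the gain is always large.** If the t-test is on change scores and 25.7 is the score SD, the gain at r = 0.7 is only from 95% to 97.5%.
- **That the stated 80% can hold for only one type of score.** At r = 0.5 it holds for both.
- **That chance baseline imbalance is a further problem.** At 75 per arm the baseline difference has SD 25.7 × √(2/75) = 4.20, but only r times the imbalance carries into a six-month comparison (SD about 2.1 at r = 0.5). That part is already inside the standard error on which the 80% rests, so it is the same precision loss counted again.
- **That randomisation is within centre, so centre must be in the model.** The article says the trial runs in two centres and that half are randomly assigned. It does not state stratification.

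**Conclusion.** The point holds as a free improvement. The named between-arm test leaves the baseline score out as a covariate, although it is collected for the result variables. Taking 25.7 as the score SD, replacing the six-month t-test by ANCOVA raises power at 73 per arm from 80% to between 84% and 97.5% for assumed correlations of 0.3 to 0.7. Across that range ANCOVA is ahead whether the t-test is applied to six-month or to change scores, and whichever SD 25.7 describes. The recommendation therefore does not depend on knowing r; only the size of the gain does. The planned t-test is not biased, and the 73 per arm is correctly computed for it. The absolute powers are best read as a comparison between methods, since dropout and therapy-group clustering are left out.

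**What to change.** In the Statistical analysis section, replace the between-arm t-test for quantitative outcomes by a linear model of the six-month score on arm and the baseline value of the same score. Report the adjusted difference in means with its 95% CI. Centre may be added as a further covariate, but this is optional. In Study population, add one sentence saying whether 25.7 is the SD of the score or of its change.

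The cost is a change of wording before the analysis starts. No further participants, visits or measurements are needed, and the statistical package already named can fit the model.

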**Methods/Design:**

This is multicentre clinical trials study, randomized in two parallel groups, carry out in two PHC, Study population: 150 caregivers will be included by consecutive sampling and they will be randomized the half to experimental group and the other half to control group. They provide mostly all the assistance to care-dependent familiars receiving attention in PHC Centers.

Measurements: Each caregiver will be evaluated on a personal interview. The caregivers' assessment protocol: 1) Assessment of different socio-demographic related to care, and caregiver's personal situation. 2)Care-dependent individuals will also be assessed by Barthel Index and Pfeiffer Questionnaire (SPMSQ). 3)Change in caregivers will be the principal measure: family function (Family APGAR Questionnaire), burden short questionnaire (Short Zarit Burden Interview), quality of life (Ruiz & Baca: 1993 Questionnaire), the Duke-UNK Functional Social Support Questionnaire, the General Health Questionnaire-12, and changes in Dysfunctional Thoughts about caring. 4) Intervention implementation measures will also be assessed.

Intervention: A psychotherapeutic intervention will be 8 sessions of 90 minutes in groups. This intervention has been initially developed for family caregivers of patients with dementia.

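### Change is the principal measure, yet the only tests named for repeated measures are within-arm; effectiveness should be tied to the between-arm six-month difference, adjusted for baseline

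*Protocol article*

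**What the plan says.** All of this is in the protocol article.

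- **Principal measure** (Abstract, Methods/Design): "Change in caregivers will be the principal measure".
- **Timing** (Result Variables): "Variables will be assessed before the intervention and after six months of the first assessment". There are thus two measurements per caregiver, one of them at baseline.
- **Allocation** (Study population): "One half will be randomly assigned to the trial group and the other half to the control group in a waiting list format".
- **Sample size** (Study population): the target is "a difference of or superior to 12 units on the Ruiz-Baca's quality of life questionnaires between the intervention group and its control", and the conditions are "With an estimated alpha risk 0.05 and a beta risk 0.20 in a bilateral contrast". The assumed SD is 25.7, giving 73 per arm; 150 caregivers are planned, or 75 per arm.
- **Between-group test** (Statistical analysis): "The Student t-test for independent samples will be used to compare the means for the two groups". No outcome, time point or scale is named. The sentence stands in a paragraph that opens with the description of socio-demographic characteristics.
- **Change over time** (Statistical analysis, next sentence): "the analysis of repeated measures will be based on the McNemar test for qualitative data and the Student t-test for paired data".
- **Impact** (Statistical analysis): "Analyzing the impact of the intervention will be carried out through intent to treat analysis". This says who is analysed, but names no contrast or model.

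**The concern.** The paired t-test and McNemar's test ask whether an arm differs from its own baseline. In a waiting-list trial the control arm exists because caregivers may change over six months for other reasons, such as natural course or repeated questionnaires. A before-after test includes that change in its answer. Setting a significant result in one arm beside a non-significant result in the other does not test the difference between arms and does not hold the 5% error rate.

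The tests attached to the principal measure are therefore not the contrast for which the trial is powered. The test that could be that contrast is not attached to the outcome. An analyst is left free to choose between six-month scores, change scores and within-arm results after seeing the data. Baseline scores, which are collected anyway, are not used for precision.

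**Working it through.** **1. The plan's own sample size.** Inputs from Study population: difference 12, SD 25.7, two-sided alpha 0.05, power 0.80.

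n per arm = 2 × (1.960 + 0.842)² × 25.7² / 12² = 72.001 before rounding of the normal quantiles shown, rounded up to **73**. This matches the article. Power at 73 per arm is 0.805 (normal) or 0.800 (noncentral t). The figure is that of a two-sample comparison between arms.

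**2. What would happen if effectiveness were read from the within-arm tests.** This decision rule is assumed; the article does not state it. Other assumptions: 75 per arm, SD 25.7 at both times, correlation r between baseline and six months (not given in the article), and the same true improvement d in both arms, so no treatment effect.

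- SD of change = 25.7 × √(2(1 − r)).
- p = probability that one arm shows a significant improvement, from the noncentral t with 74 df and noncentrality d × √75 / (SD of change).
- P(only the intervention arm significant) = p(1 − p). The maximum is 0.25, at p = 0.5.

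| r | SD of change | d = 0 | 2 | 4 | 6 | 8 | 12 |
|---|---|---|---|---|---|---|---|
| 0.5 | 25.70 | 2.4% | 8.8% | 19.5% | 25.0% | 18.3% | 2.1% |
| 0.6 | 22.99 | 2.4% | 9.9% | 21.7% | 23.9% | 13.1% | 0.6% |
| 0.7 | 19.91 | 2.4% | 11.7% | 24.1% | 19.7% | 6.5% | 0.1% |

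The peak falls at a shared improvement of about 5.9, 5.3 and 4.6 units respectively. For comparison, a valid two-sided 5% test favours the intervention falsely in 2.5% of null trials.

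**3. Simulation check** (40,000 null trials, r = 0.6). With a shared improvement of 5.27 units, only the intervention arm was significant in 25.1% of trials. An independent t-test between arms was significant in 5.1% on change scores and 5.0% on six-month scores. With no change the figures were 2.5%, 4.9% and 5.0%. The between-arm test keeps its level on either scale.

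**4. What baseline adjustment gains.** Taking 25.7 as the SD of the six-month score, ANCOVA has residual variance 25.7² × (1 − r²), so the fraction removed is r². Standard error of the difference = residual SD × √(2/73); noncentrality = 12 / SE; power from the noncentral t.

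| Analysis | Variance removed | Residual SD | SE | 12/SE | Power, 73 per arm |
|---|---|---|---|---|---|
| Unadjusted six-month score | 0 | 25.70 | 4.254 | 2.821 | 0.800 |
| ANCOVA, r = 0.5 | 25% | 22.26 | 3.684 | 3.257 | 0.899 |
| ANCOVA, r = 0.6 | 36% | 20.56 | 3.403 | 3.526 | 0.939 |
| ANCOVA, r = 0.7 | 49% | 18.35 | 3.038 | 3.950 | 0.975 |

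A t-test on change scores has relative variance 2(1 − r): 1.0 at r = 0.5 and 0.6 at r = 0.7, against 0.75 and 0.51 for ANCOVA. ANCOVA is the more precise of the two at both values.

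**The case against.** The strongest reply is that a valid between-arm test is already in the plan. The independent-samples t-test stands in the sentence just before the paired tests. On six-month or change scores it tests the intervention at the stated level. The chi-squared test can do the same for a binary outcome. The sample size is built on a between-arm difference, and intention to treat makes most sense for a comparison of randomised arms. On that reading the paired tests are supplementary description, and in a condensed article the exact scale of the t-test may be left to a fuller document.

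Most of this stands. A reader might infer that the plan contains no test of the intervention, or that the investigators will claim success when one arm improves significantly and the other does not. The article supports neither. A reader might also quote a false-finding rate of up to half. That counts trials in which only the control arm improves, which would not be reported as a benefit, and it needs a shared improvement near the worst value.

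What does not fall away is that the article is not silent on change. It names a method for repeated measures, and that method cannot estimate the randomised effect. It also leaves the valid test unlinked to the principal measure.

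**Conclusion.** The point holds as a mismatch that costs nothing to repair, and is less serious than an error that would invalidate the trial. Three things are firm: change is the principal measure, the tests named for repeated measures are within-arm only, and the trial is sized on a between-arm contrast. The between-arm t-test is sound but is not tied to the six-month or change score.

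The risk from within-arm reading is conditional on a rule that the article does not state. Its ceiling is 25% for a result favouring the intervention only; it is about 2.4% with no change in either arm, and 0.1–2.1% with a shared change of 12 units at r = 0.5–0.7.

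The gain from adjustment is 25–49% of the variance, with power of about 0.90–0.98 instead of 0.80 at 73 per arm. It rests on an assumed correlation of 0.5–0.7 and on 25.7 being the SD of a score, not of a change. If 25.7 were the SD of change, the reduction relative to a change-score t-test would be (1 − r)/2, that is 15–25%.

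**What to change.** In Statistical analysis:

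- State that effectiveness is judged by the difference between arms in six-month score, adjusted for the baseline score (ANCOVA), by randomised group, with a 95% CI.
- For binary outcomes, such as family APGAR below 7, use logistic regression of six-month status on arm and baseline status.
- Report within-arm changes descriptively, as mean change with CI, and say that the paired t-test and McNemar's test are not used to judge the intervention.

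The cost is two or three sentences. Both measurements are already planned, the models are standard, and the sample size need not change: 73 per arm for 12 units remains sufficient and becomes conservative to the extent that baseline predicts the six-month score.
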